### Interventions

#### DrinkingLess

*DrinkingLess* is an evidence-based cognitive behavioural internet intervention [25]. Since most visitors of the *DrinkingLess* website were found to complete the first two out of four modules of the intervention [31], and these modules were also deemed most important to prepare participants for the CBM interventions, only these modules are offered in the current study. The modules include personalised feedback on alcohol use and its consequences, and setting personal goals related to alcohol use (see [25,31] for more information).

#### CBM interventions

Each CBM session consists of three tasks: attentional bias retraining, alcohol/no-go training, and approach bias retraining. Each task consists of three phases: a practice block, an assessment block (48 trials), and a CBM block (120 trials). The purpose of the assessment block is to measure the strength of the bias at the start of every session, to examine whether biases decrease as a result of CBM training. During the CBM block, participants will receive either the experimental or the placebo version of the specific CBM version. A large set of pictures of alcoholic drinks, non-alcohol drinks and neutral objects was created specifically for this study, the validity of which is currently studied in our lab. Each trial starts with a fixation cross which is presented in the middle of the screen for 500 ms. The inter-trial interval is 500 ms. Since some varieties of CBM have been perceived as boring and participants have trouble seeing how CBM could help them reduce their problems [32], special attention was given to the treatment rationale. Furthermore, a game-like system of earning points was included in order to keep participants motivated to respond accurately and quickly and to complete all CBM sessions.

#### Attentional bias retraining

Attentional bias is assessed and trained using the visual probe task [16,33,34]. In this task, a picture of an alcoholic and a picture of a non-alcohol beverage are presented next to each other on the screen for 500 ms. When the pictures disappear, a small arrow pointing up or down appears at the location of one of the pictures. Participants are instructed to respond to the direction of the arrow, by pressing the corresponding arrow key on the keyboard. In the assessment block, the arrow replaces the picture of the alcoholic beverage (alcohol trials) and the picture of the non-alcoholic beverage (non-alcohol trials) equally often. Attentional bias for alcohol is computed by subtracting response times (RTs) on alcohol trials from those on non-alcohol trials. In the CBM block, participants in the experimental condition will be trained to direct their attention away from alcoholic beverages towards non-alcoholic beverages, by exposing them only to non-alcohol trials, while participants in the placebo condition receive 50% alcohol and 50% non-alcohol trials (as in the assessment block). For an example of a trial in the attentional bias retraining, see Figure 3.

**Figure 3 F3:**
[figure not shown]
Example of a trial in the attentional bias retraining.

#### Alcohol/no-go training

Alcohol related memory bias (positive associations with alcohol) is measured and trained using the alcohol/no-go task [11]. In this task, a picture of an alcoholic or non-alcoholic beverage is presented for 1500 ms, together with a go (i.e. the letter ‘p’) or no-go cue (‘f’) which is displayed randomly in one of four corners of the picture. Participants are instructed to respond to the presented letter, by pressing the spacebar as quickly as possible when they see the letter ‘p’, and doing nothing (wait until picture disappears) when they see the letter ‘f’. The combination of the letter and the response (p = press and f = inhibit, versus f = press and p = inhibit) is counterbalanced across participants. In the assessment block, the pictures of alcoholic and non-alcoholic beverages are presented equally often with a go and with a non-go cue. Alcohol/go bias is computed by subtracting RT’s on alcohol/go trials from those on non-alcohol/go trials. In addition, the number of errors (incorrect go responses) can be compared between alcohol and non-alcohol no-go trials. In the CBM block, participants in the experimental condition will be trained to inhibit their response to alcohol, by exposing them only to alcohol/no-go trials and non-alcohol/go trials, while for participants in the placebo condition there is no relation between the content of the picture and the required response. For an example of a trial in the alcohol/no-go training bias retraining, see Figure 4.

**Figure 4 F4:**
[figure not shown]
Example of a trial in the alcohol/no-go training.

#### Approach bias retraining

Approach bias is measured and trained with the modified Approach-Avoidance Task (AAT [22]). In this intervention, a picture of an alcoholic or non-alcoholic beverage is presented, which is tilted 3 degrees to the left or right. Participants are instructed to respond to the format of the picture, by pushing all pictures tilted to the right away from them, and pulling all pictures tilted to the left towards them. The combination of the format of the picture and the response (left = push and right = pull, versus left = pull and right = push) is counterbalanced across participants. Picture size gradually increases when the pull-key is pressed, while it decreases when the push-key is pressed. In the assessment block, the pictures of alcoholic and non-alcoholic beverages are presented equally often in push and in pull format. Approach bias for alcohol is computed by comparing RTs for push, pull, alcohol and non-alcohol trials ((alcohol/push - alcohol/pull) - (non-alcohol/push - non-alcohol/pull)). In the CBM block, participants in the experimental condition will be trained to avoid alcohol, by exposing them only to alcohol/push and non-alcohol/pull trials, while for participants in the placebo condition there is no relation between the content of the picture and the required response. For an example of a trial in the alcohol/no-go training bias retraining, see Figure 5.

**Figure 5 F5:**
[figure not shown]
Example of a trial in the approach bias retraining.

### Baseline measures

Eligibility for the study will be assessed with the TLFB [35] and the AUDIT [30]. Lifetime alcohol and drug use and use during the past month is assessed, as well as history of alcohol use problems (alcohol scales of the European Addiction Severity Index, EuropASI [36]). Participants indicating they smoked during the past month will fill out the Fagerström Test for Nicotine Dependence (FTND [37]). Motivation to change alcohol use is measured with the Readiness to Change Questionnaire (RCQ [38]). Symptoms of depression and anxiety are measured with the Beck Depression Inventory-II (BDI-II [39]), and the Spielberger State-Trait Anxiety Inventory (STAI [40]), respectively. High trait sensitivity, which is correlated with genes related to susceptibility to both positive and negative environmental influences [41,42], is measured as a possible predictor of the changeability of automatic biases (using a short version of the High Sensitive Personality Child Questionnaire (HSC [43]).

A computerised version of the Self-Ordered Pointing Task (SOPT [44] is used to assess working memory capacity. In this task, participants are presented with a grid of pictures of concrete objects, and are instructed to click on each picture with the computer mouse. There are two rules: one can only click each picture once, and one cannot click on the same location twice in a row. The task starts with a practice block of 4 pictures, and proceeds with 5 consecutive test blocks with 6, 8, 10, 12, and 12 pictures. The outcome is the correct number of unique pictures selected during the test blocks.

The classical [45] and alcohol [46] Stroop are used to assess response inhibition and attentional bias, respectively. The task starts with a practice block, in which participants have to learn the correct key-colour combination. In the next block (alcohol Stroop), participants have to identify the colour of 7 alcohol-related words (e.g. wine, whiskey), and 7 matched neutral words (office supplies). Each word is presented in four colours, resulting in 56 trials. The final block consists of a classical Stroop task of 56 trials, with 8 congruent trials (red in red), 24 incongruent trials (red in green), and 24 neutral trials (%%% in green). An overview of all measurement instruments and assessments is presented in Figure 6.

**Figure 6 F6:**
[figure not shown]
Measurement instruments.

### Primary and secondary outcome measures

The main outcome measure, the change in number of drinks consumed in the past 14 days three months after the intervention compared to baseline, will be assessed using the TLFB method [35]. Secondary outcome measures are: changes in automatic cognitive biases as assessed with the attentional bias, alcohol/no-go and approach bias tasks described above. Generalisation effects of attentional bias and approach bias training to other measures will be assessed with the alcohol Stroop task (described above) and the brief Implicit Association Task (bIAT, [47,48]), which is used to measure the strength of both approach associations and positive (valence) associations with alcohol. In the bIAT, participants are required to decide whether or not the exemplar word in the middle of the screen belongs to one or two focal categories at the top of the screen, by pushing the designated ‘yes’ or ‘no’ buttons (‘e’or ‘i’) on the keyboard. As in the study of Menatti et al. [47], the typical 7 block structure of the IAT was maintained, but with fewer trials per block. In the first block (12 trials) names of alcoholic (wine, beer, vodka) or non-alcoholic drinks (coke, water, juice) have to be classified as either belonging to the category ‘alcohol’ or not. In the second block (12 trials) exemplars have to be classified as either pleasant (funny, cheerful, sociable) or not (nauseous, sad, tired). In the third block (12 trials) and fourth (24 trials), the target (alcohol) and attribute (pleasant) categories are combined. In the fifth block (12 trials), the reversed attribute category, unpleasant, is practiced and then combined with the target category (alcohol) in the sixth (12 trials) and seventh block (24 trials). The approach bIAT follows the same structure, with the attributes ‘approach’ (grab, touch, take) ‘avoid’ (let go, avert, ignore). The order of the two versions of the bIAT, as well as the order of the combined blocks within the bIAT, and the contingency between the response (yes/no) and the buttons (i/e) is counterbalanced across participants. The outcome measure is the standardised difference in latencies (*D* score*)* between the different combined blocks.

Other secondary measures are: the percentage of participants drinking within the limits for sensible drinking [49]: a maximum of 21 standard units of alcohol per week for men, and 14 units a week for women) and binge drinking (drinking >5 glasses on one day), both measured with the TLFB [35]. Alcohol-related problems will be assessed with the AUDIT [30], which was adapted to a three month version in order to enhance its sensitivity to changes within the follow-up period of the study. Craving will be measured with the Desires for Alcohol Questionnaire (DAQ [50]), and by asking participants how much they want to drink each of three pictured alcoholic and non-alcohol beverages at this moment on a 10 point scale. Self-efficacy will be assessed with the Brief Situational Confidence Questionnaire (BSCQ [51]), in which participants are asked to indicate on a visual analogue scale how much confidence they have that they will not drink heavily in eight specific situations. Quality of life will be measured with the EQ-5D [52]. The economic costs stemming from health care uptake and productivity losses associated with problematic alcohol use will be assessed with the Trimbos/iMTA Questionnaire for Costs associated with Psychiatric illness (TiC-P [53]).

### Sample size

G*Power 3.1.5 [54] was used to calculate the sample size for a power of 0.8 for each main effect or interaction (all Numerator *df* = 1), at an alpha of 0.05. Based on a meta-analysis of internet self-help interventions for problem drinkers a medium effect size (*f* = 0.25) would be expected [2], but the effect size may be reduced by the active control conditions and the two modules of the *DrinkingLess* intervention that all participants receive. A small-to-medium effect size of *f* = 0.15 was therefore specified, for which the required sample size is 351 (see Figure 7).

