### Randomisation

Participants meeting the inclusion criteria will be automatically assigned to one of the 8 intervention conditions with an equal likelihood, using the method of minimisation [55] in order to balance for gender and AUDIT risk level (scores 8–19 versus >19). Participants will be randomly allocated to one of the conditions to which the fewest participants of their gender and AUDIT level have so far been assigned. Intervention allocation will be corrected for excluded participants. Participants will be excluded if (a) they do not complete the baseline assessment including *DrinkingLess*, or (b) if they indicate that they want to discontinue the study.

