The main strength of this study is also its main limitation: the effectiveness of CBM might be threatened by its web-based delivery. First, the less controlled home environment might pose several distractions, both online (incoming e-mails, other browser windows), and ‘offline’ (television, phone calls), which could confound the RT-based CBM interventions. To this end, participants are reminded at the start of each CBM session of the importance of concentration for the effectiveness of the training. The feasibility of web-based CBM is supported by a recent study on attentional bias retraining in social anxiety, which found error rates and reactions times comparable to those in a lab-based setting, though no evidence was found of training effects [61]. Second, online interventions are commonly faced with high attrition rates [62]. Therefore, treatment adherence is encouraged in five ways: 1) by automatic e-mails that are sent to invite and remind participants of CBM sessions 2) the possibility of e-mail contact with the first author in case participants have questions or encounter technical difficulties 3) the attention that was paid to the intervention rationale 4) the inclusion of motivating features to the CBM interventions 5) a lottery system in which participants who complete the follow-up assessments can win gift vouchers. Taken together, the possible threats presented by the web based setting of this study are outweighed by the possibilities offered by internet-delivered CBM, which, if proven effective, could easily be implemented as a low threshold, early intervention for problem drinkers.

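### The sample size of 351 is a count of observed 3-month outcomes with no allowance for loss; if it is the number randomised, power falls below the stated 0.8

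*Protocol article*

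**What the plan says.** The Sample size section uses G*Power "to calculate the sample size for a power of 0.8 for each main effect or interaction", "at an alpha of 0.05" with one numerator degree of freedom. A medium effect from earlier internet trials is cut because the controls are active and everyone receives part of DrinkingLess: "A small-to-medium effect size of *f* = 0.15 was therefore specified". The section ends there: "for which the required sample size is 351". Loss to follow-up is not mentioned.

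The Discussion observes that "online interventions are commonly faced with high attrition rates" and answers that "treatment adherence is encouraged in five ways". It gives no rate and does not return to the sample size.

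The Clinical evaluation section commits to intention to treat, with missing endpoints filled in by the EM algorithm. The Randomisation section says that participants are "automatically assigned to one of the 8 intervention conditions with an equal likelihood". It corrects the allocation for people who do not finish baseline or who say that they wish to stop. No recruitment target other than 351 appears in the text shown.

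**The concern.** A power calculation of this kind returns the number of participants whose outcomes enter the test. The primary outcome is the change in 14-day drinking from baseline to three months after a programme of about five weeks, delivered unsupervised over the web. Some 3-month values will be missing, and the plan provides for that. If 351 is nevertheless the number entered, the power of 0.8 claimed for each main effect and interaction is not reached.

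What is at stake is how a null result is read. A non-significant training effect would be judged against 80% power at f = 0.15, whereas the effect that the trial could detect with that power would be larger.

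**Working it through.** **Inputs from the article.** Power 0.8, alpha 0.05, numerator df 1 and f = 0.15 (Sample size); eight cells with equal allocation (Randomisation). For a two-level factor split equally, d = 2f = 0.30.

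**Input not in the article.** The proportion without a 3-month outcome. I use 10% to 50% as an assumed range.

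**1. Reproduce the stated figure.** The power of the fixed-effects F test is P(F′ > F_crit), where F′ is noncentral F with df1 = 1, df2 = N − 8 and λ = f²N, and F_crit is the 95th percentile of the central F.

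- N = 350: λ = 0.0225 × 350 = 7.875, df2 = 342, power 0.7991.
- N = 351: λ = 0.0225 × 351 = 7.898, df2 = 343, power 0.8002.

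So 351 is the smallest N that reaches 0.80, and it is reproduced exactly with all outcomes observed. Using two groups instead of eight also gives 351. A one-sided equivalent would give 277, so the calculation is the usual two-sided one.

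**2. Look for an allowance elsewhere.** The cut in f is justified by the active controls and the shared modules, not by attrition. The correction in the Randomisation section covers baseline non-completers and declared withdrawals. It does not cover participants who simply stop responding.

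**3. Power if 351 are randomised.** Put n = 351(1 − loss) into the same formula. The last column is 351/(1 − loss), rounded up.

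| Assumed loss | n observed | λ = 0.0225n | Power at f = 0.15 | f detectable at 80% power | Number to randomise to keep 351 |
|---|---|---|---|---|---|
| 0% | 351 | 7.90 | 0.80 | 0.150 | 351 |
| 10% | 316 | 7.11 | 0.76 | 0.158 | 390 |
| 20% | 281 | 6.32 | 0.71 | 0.168 | 439 |
| 30% | 246 | 5.54 | 0.65 | 0.179 | 502 |
| 40% | 211 | 4.75 | 0.58 | 0.194 | 585 |
| 50% | 176 | 3.96 | 0.51 | 0.212 | 702 |

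Even 5% loss (n = 333) gives 0.78.

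**4. Does EM imputation bring back the 351?** This was simulated with N = 352, a baseline–outcome correlation of 0.5, outcomes missing completely at random, and one conditional-mean fill-in from baseline, with 3,000 replicates per setting.

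- Fill-in model including the design cells: the rejection rate under the effect stays at about 0.82 (20% loss) and 0.83 (40%), but type I error rises to about 0.09 and 0.19. The apparent power comes from treating filled-in values as data.
- Fill-in model without the cells: type I error stays near 0.05, and power is about 0.68 and 0.51.

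The simulation used baseline only and no other visits.

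**5. Sensitivity to what f refers to.** The table takes f = 0.15 on the change score. If f is instead on the single-time-point scale, then on the change score it becomes 0.15/√(2(1 − r)), where r is the baseline–follow-up correlation.

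- r = 0.3: f = 0.127; power 0.66 with no loss.
- r = 0.5: f = 0.150; the table is unchanged.
- r = 0.6: f = 0.168; power 0.88 with no loss, 0.80 at 20% loss.
- r = 0.7: f = 0.194; power 0.95 with no loss, 0.80 at 40% loss.

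The article states no r, so neither a reserve nor a deficit can be claimed from this source.

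**The case against.** The strongest reply is that nothing has been miscalculated and that the article never says 351 will be randomised. The required number from such a calculation is by construction a number analysed. On that reading the stated power is correct, and only the recruitment figure is unstated. A condensed article may leave that figure to the full protocol, and the flowchart and the G*Power figure are not shown. This stands, and it makes the shortfall conditional. It does not remove the need to say which number 351 is.

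A reader might also infer that the plan forecasts high attrition for this trial. The text does not support that. The remark concerns online interventions in general and comes with countermeasures. Those measures are presented as supporting adherence, and only the lottery is tied to completing follow-up. A participant who skips sessions can still supply the 3-month outcome under intention to treat.

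It can further be argued that post-intervention, 6-month and 12-month data could inform a missing 3-month value, so that some information is recoverable. That is possible in principle, but the amount depends on correlations that the article does not give. The same holds for any suggestion that baseline adjustment would make good the loss at no cost.

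**Conclusion.** The point holds conditionally and should be fixed. It is a gap in what 351 is said to represent, not an error of arithmetic. The figure is the exact zero-loss requirement, and no allowance for loss appears in the text shown, although the same article names attrition as a threat and plans for missing endpoints.

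If 351 is the number randomised, power for each main effect or interaction is below 0.8 at any appreciable loss: between 0.76 and 0.51 over the assumed 10% to 50%, with detectable f between 0.158 and 0.212. This rests on the assumed loss rates, on f = 0.15 applying to the change score, and on no recovery of information from other measurements.

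A reader might go further and conclude that the trial certainly lacks its stated power. The article does not establish that, because it fixes neither the number randomised nor an attrition rate.

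**What to change.** In the Sample size section:

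1. State that 351 is the number of participants with an observed 3-month Timeline-Follow-Back outcome.
2. State the attrition assumed at three months and its basis.
3. Give the number to be randomised, with the power or detectable f that follows. If 351 are randomised and 20% loss is assumed, for example: power 0.71 at f = 0.15, or 0.80 at f = 0.168. If 351 outcomes are to be kept at that loss, the number to randomise is 351/0.8 = 439.
4. Say whether f refers to the change score. If recovery of information from baseline or other visits is to be counted, state the correlation assumed.
5. Do not count values filled in by a single EM imputation towards the 351.

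Restating the power is a wording change, and the stated power becomes less favourable if 351 is the number randomised. Raising enrolment instead costs the extra participants shown in the table: 39 at 10% loss (390 − 351), 88 at 20% (439 − 351) and 234 at 40% (585 − 351).

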**Figure 7 F7:**
[figure not shown]
Sample size calculation using G*Power 3.1.5.

### Randomisation

Participants meeting the inclusion criteria will be automatically assigned to one of the 8 intervention conditions with an equal likelihood, using the method of minimisation [55] in order to balance for gender and AUDIT risk level (scores 8–19 versus >19). Participants will be randomly allocated to one of the conditions to which the fewest participants of their gender and AUDIT level have so far been assigned. Intervention allocation will be corrected for excluded participants. Participants will be excluded if (a) they do not complete the baseline assessment including *DrinkingLess*, or (b) if they indicate that they want to discontinue the study.

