**Methods/design:**

The effectiveness of 12 sessions of CBM will be examined among problem drinkers aged 18–65 who are randomly assigned to one of the eight CBM conditions, after completing two modules of a validated cognitive behavioural intervention, *DrinkingLess*. The primary outcome measure is the change in alcohol use. It is expected that, for each of the CBM interventions, participants in the real CBM conditions will show a greater decrease in alcohol use than participants in the placebo conditions. Secondary outcome measures include the percentage of participants drinking within the limits for sensible drinking. Possible mediating (change in automatic biases) and moderating (working memory, inhibition) factors will be examined, as will the comparative cost-effectiveness of the various CBM strategies.

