### Clinical evaluation

All analyses will be conducted in agreement with the intention to treat principle, as per the CONSORT statement [56]. To that end, missing endpoints will be imputed using the EM algorithm [57]. The main effects and interaction effects of the CBM interventions on the primary and the continuous secondary outcome measures will be analysed with a 2 (attentional bias retraining: active/placebo) × 2 (alcohol/no-go training: active/placebo) × 2 (approach bias retraining: active/placebo) × 2 (time: pre-intervention/3 month follow-up) repeated measures ANOVA.

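### Excluding participants who want to discontinue, with no time limit and with the allocation corrected for them, contradicts the intention-to-treat rule

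*Protocol article*

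**What the plan says.** Protocol article, Randomisation: participants who meet the inclusion criteria are "automatically assigned to one of the 8 intervention conditions with an equal likelihood, using the method of minimisation", balancing gender and AUDIT level. Each is "randomly allocated to one of the conditions to which the fewest participants of their gender and AUDIT level have so far been assigned". The section then states "Intervention allocation will be corrected for excluded participants" and gives two grounds for exclusion: (a) that "they do not complete the baseline assessment including" DrinkingLess, and (b) "if they indicate that they want to discontinue the study". Neither ground carries a time limit.

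Protocol article, Clinical evaluation: "All analyses will be conducted in agreement with the intention to treat principle", and missing endpoints are imputed by the EM algorithm to serve that aim.

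Protocol article, Abstract (Methods/design): participants are "randomly assigned to one of the eight CBM conditions, after completing two modules of a validated cognitive behavioural intervention".

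**The concern.** Under intention to treat, a participant once assigned is analysed in the assigned condition. A wish to leave the study can arise after assignment and can be a response to the training received. Removing people on that ground leaves groups that are no longer the ones randomisation created. The article expects losses: its Discussion notes that attrition in online interventions is commonly high, and the CBM interventions section notes that some CBM has been found boring. What is at stake is who is analysed for the primary outcome, the change in 14-day drinking from baseline to three months after the intervention.

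The order of events is also unclear. Rule (a), tied to a correction of the allocation, makes sense only if people are assigned before they finish DrinkingLess. The abstract says the opposite.

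**Working it through.** **1. Does rule (b) reach assigned participants?** The text sets no time limit, and correcting an allocation presupposes that one has been made. It therefore does. This is an inference, but a firm one.

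**2. Can the two sections both be followed?** A participant excluded under Randomisation cannot also be retained with an imputed endpoint under Clinical evaluation, unless exclusion means only removal from the minimisation counts. The article does not say that it means this.

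**3. The design effect.** Inputs from Sample size: f = 0.15, alpha 0.05, power 0.80, numerator df 1. With a noncentral F, 8 groups, denominator df N − 8 and λ = f²N, the smallest N that reaches 0.80 is 351 (λ = 0.0225 × 351 = 7.90, power 0.8002). The stated 351 is reproduced and this point does not affect it. For two equal groups d = 2f = 0.30 SD.

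**4. Bias if assigned discontinuers are left out.** Let q be the proportion excluded in an arm, and D the mean change in drinking among the excluded minus that among the retained, in SD of change. D must refer to change: the primary outcome is a change and the model has time as a factor, so a stable difference in drinking level cancels.

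- Retained mean = arm mean − q × D.
- With the same D in both arms, the bias in the contrast has size p × D, where p is the difference in q between active and placebo.
- Assumed q of 20% and 10%, so p = 0.10: D = 0.5 gives 0.05 SD, and D = 1.0 gives 0.10 SD.
- Share of the design effect: 0.05/0.30 = 17%; 0.10/0.30 = 33%.

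**5. False positives under those assumptions.** Retained: 351/2 × (0.80 + 0.90) = 298. Standard error = √(4/298) = 0.116 SD. A two-sided 5% normal test then rejects a true null with probability 7.2% at a bias of 0.05 SD and 13.9% at 0.10 SD.

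**6. Equal exclusion rates do not guarantee safety.** In a simulation with no true effect, 351 participants and a base exclusion rate of 20% in both arms:

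| Dependence of exclusion on outcome | Bias (SD) | False positives |
|---|---|---|
| None | 0.00 | 4.7% |
| Active arm only, log-odds slope 0.5 per SD | 0.10 | 14% |
| Active arm only, log-odds slope 1 per SD | 0.20 | 40% |

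The rate and the slopes are assumptions.

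**7. What the correction does to allocation.** Assume 30% exclusion in one factor's four active cells and 10% in its four placebo cells. Corrected counts tend to equalise those retained: 0.70A = 0.90P with A + P = 351, so A = 351 × 0.90/1.60 = 197 and P = 154. Simulated minimisation in four gender-by-AUDIT strata gives the same, 197 and 154, against about 175 and 176 when the counts are not corrected. Those retained number about 138 and 139. So discontinuers are replaced and the numbers ever assigned become unequal.

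**The case against.** The Randomisation section concerns allocation, and the article never says in so many words that the excluded leave the analysis set. They might be dropped only from the minimisation counts and still be imputed. That reading is possible, so removal from the analysis cannot be stated as fact. It does not settle the matter, because nothing in the text adopts it.

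A reader might infer that letting dropout steer later allocation biases the comparison by itself. It does not: ties are broken at random, and any bias comes from omitting assigned discontinuers. A reader might also infer that correction necessarily hides differential attrition. Step 7 shows otherwise: the numbers ever assigned become unequal, so a flow diagram that reports them would reveal it.

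Rule (a) is unlikely to bias anything. Under Participants and procedure, the first CBM session is offered the day after baseline and DrinkingLess, so these losses precede any exposure to a condition.

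Leaving the study is not the same as stopping the training. Some discontinuers will withdraw consent for data collection and have no outcome under any rule. EM imputation may not remove all the bias if they leave for reasons tied to unseen outcomes, so the fix need not recover the whole of p × D.

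Finally, active and placebo versions use the same tasks with different trial contingencies and are designed to keep participants blind. Nothing in the article supports a 10-point gap in exclusion in particular.

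**Conclusion.** The contradiction stands. As written, rule (b) and the correction of allocation remove and replace randomised participants for a post-assignment reason, and this conflicts with an explicit intention-to-treat rule for all analyses. The order of assignment and DrinkingLess is stated inconsistently; that needs reconciling but is a minor matter.

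The size is conditional. If assigned discontinuers are omitted, the bias is about p × D: 0.05 to 0.10 SD, or 17% to 33% of the design effect, for an assumed p of 10 points and D of 0.5 to 1.0 SD of change. The article gives no discontinuation rate and no D. It could be zero if exclusion is unrelated to outcome, and larger if the relation differs by arm. The documents do not support saying that the analysed groups will certainly be only those who stayed.

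**What to change.** - Trigger assignment when baseline and both DrinkingLess modules are recorded as complete, in line with the abstract.
- Limit exclusions (a) and (b) to the time before assignment, and delete the correction of allocation for anyone already assigned.
- Keep every assigned participant in the minimisation counts, in the assigned condition and in the intention-to-treat analysis.
- Keep inviting discontinuers to follow-up unless consent for data collection is withdrawn, and treat their missing outcomes as missing data.
- Report the numbers ever assigned and discontinued by condition.

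The cost is a change to the automated allocation trigger and counter, plus wording. The downside is that the numbers of completers per cell may be slightly less equal.
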